### Trial design {8}

#### Study design

The trial is a pragmatic, multi-centre, three-arm parallel-group randomised controlled trial using re-randomisation.

The hypothesised benefit of the TLI systems may be due to either a closed undisturbed culture system or the use of morphokinetic parameters for embryo selection or both. Hence, a three-arm study design is necessary to answer the research question and define the contributions of both the variables involved.

The trial will compare the results of the following:
Intervention 1: incubation and assessment of embryos using TLI systems (morphokinetic parameters + undisturbed culture + morphological assessment)Intervention 2: incubation of embryos in undisturbed culture and standard embryo assessment (undisturbed culture + morphological assessment)Control: standard care (morphological assessment alone)

The design of this trial will be pragmatic. It will allow centres to use a TLI system of their choice. The trial tests the basic premise that undisturbed culture and/or addition of morphokinetic parameters to standard embryo assessment improves outcomes in IVF/ICSI treatment. It does not aim to test nor validate individual TLI systems and algorithms. The trial will use the manufacturer’s algorithm for morphokinetic parameters as a minimum standard to ensure quality control and external validity to the study. It will allow centres to develop more sophisticated centre-specific algorithms by incorporating further parameters into the basic model recommended by the manufacturer. It is accepted that clinical protocols for IVF and laboratory conditions will vary with each centre. All clinical and laboratory elements of IVF/ICSI treatment apart from the randomised intervention will be carried out according to local centre protocols, ensuring only that there is no variation across the three study arms in culture medium and incubator settings (temperature, CO_2_ and O_2_ levels) within each centre.

Couples having IVF/ICSI treatment will be eligible for the trial. Eligible participants will be screened in the fertility clinics and invited to participate in the trial. Following informed consent from both partners, participants will be randomised in a 1:1:1 ratio to one of the three arms: TLI, undisturbed culture or standard care. Women will be followed up until either a negative pregnancy test 2 weeks after embryo transfer or to the end of their pregnancy following a positive pregnancy test.

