### Sample size {14}

#### Sample size

The sample size calculation was based upon the primary outcome of live birth. With a 5% overall significance level (2.5% for each of the two main treatment comparisons: TLI vs. standard care, and undisturbed culture vs. standard care), we would require 514 participant randomisations per treatment arm to detect an absolute increase in the primary outcome from 26.5 to 35.25% with 80% power. Allowing for 2% loss to follow-up or withdrawal of consent would require 525 participants per treatment arm (1575 in total).

The comparison between experimental treatment arms (TLI vs. undisturbed culture) will be performed with no impact on sample size because we will carry out this statistical test conditional to the rejection of at least one of the primary comparisons planned (TLI vs. standard care, or undisturbed culture vs. standard care). This hierarchical approach permits to maintain the overall type I error rate of 5%.

This trial uses the re-randomisation design, which was described by Kahan et al. [9]. Requirements for the re-randomisation design are as follows:
Patients are only re-randomised when they have completed the follow-up period from their previous randomisation.Randomisations for the same patient are performed independently.The treatment effect is constant across all randomisation periods.

Requirement 1 is fully satisfied, as participants will have completed their previous round of treatment before re-joining the study. Participants have an equal chance of being randomised to either of the three trial arms, regardless of their previous randomisation result, therefore satisfying requirement 2. Finally, there is no anticipated treatment effect, either in terms of efficacy or safety, from one episode to the next.

It has been demonstrated that introducing re-randomisation in a trial will not affect the validity of the statistical analysis and results [9].

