## Statistical methods

### Statistical methods for primary and secondary outcomes {20a}

Analyses will be intention-to-treat, will include all randomised participants and will analyse according to the treatment group to which they were randomised. We will analyse each participant randomisation as an independent observation (i.e. perform an independence analysis). As a sensitivity analysis, we will provide results from analyses restricted to complete cases, for comparison with results based on multiple imputation.

For each analysis, we will present the treatment effect (difference in means for a continuous outcome and an odds ratio for binary outcomes) along with a 95% confidence interval and a two-sided *p* value. Because we have two main treatment comparisons (TLI vs. standard care, and undisturbed culture vs. standard care), the significance level for the primary outcome is set at 2.5% for each treatment comparison. The primary outcome (live birth) will be analysed using logistic regression model and will be adjusted for stratification and minimisation factors and other pre-specified covariates to increase power. The stratification factor is the fertility clinic and the minimisation factors are participant’s age (< 35 years, 35–40 years, > 40 years) and type of planned first embryo transfer (fresh, frozen). Other covariates to be included in the analyses are treatment attempt, type of infertility (primary/secondary), category of infertility, duration of infertility, BMI, type of time-lapse imaging equipment, method of insemination (IVF vs. ICSI), number of retrieved oocytes and number of available embryos. A full statistical analysis plan will be developed and finalised prior to data analysis and will include full specifications on subgroup analyses.

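### Testing the two primary comparisons by Holm's procedure instead of at a fixed 2.5% each keeps the 5% overall error and gains power when both arms work; the planned split is valid, so this is a cheap improvement, not a correction

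*Protocol article*

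**What the plan says.** The Sample size section of the protocol article sets the error rate as follows: "With a 5% overall significance level (2.5% for each of the two main treatment comparisons", namely TLI against standard care and undisturbed culture against standard care. The statistical methods section {20a} repeats the rule for the analysis: "the significance level for the primary outcome is set at 2.5% for each treatment comparison". Each effect is to be presented "along with a 95% confidence interval and a two-sided" p value.

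The plan's only sequential step concerns the third comparison, TLI against undisturbed culture, which is tested only if at least one primary comparison is rejected. Of this step the Sample size section says: "This hierarchical approach permits to maintain the overall type I error rate of 5" (per cent). It gives no significance level for that third test. Nowhere does the 2.5% attached to a rejected primary comparison pass to the other one. The primary pair is therefore tested by plain Bonferroni.

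The SAP is not shown. This is still not a detail left to it, because the protocol fixes the level in two places.

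**The concern.** Once one comparison with standard care has been rejected, holding the other at 2.5% is not needed to protect the 5% overall error. Holm's procedure rejects everything the fixed split rejects and sometimes more. The plan already uses step-down reasoning to obtain the third comparison without extra participants, but does not apply it to the second primary comparison.

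What is at stake is power to confirm both arms. The TLI arm includes undisturbed culture. If undisturbed culture is what helps, both arms should beat standard care, and attributing the benefit is easier if both are confirmed.

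**Working it through.** **Inputs from the protocol**
- Live birth rates, power and size: "to detect an absolute increase in the primary outcome from 26.5 to 35.25% with 80% power"; "we would require 514 participant randomisations per treatment arm".
- Attrition: "Allowing for 2% loss to follow-up or withdrawal of consent would require 525 participants per treatment arm (1575 in total").
- Allocation: "participants will be randomised in a 1:1:1 ratio to one of the three arms", so the two comparisons share a control arm.
- Two-sided tests and no interim analyses.

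**1. The plan's own figure**

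For two proportions with pooled variance under the null and no continuity correction:

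n = [z(0.9875)·√(2p̄(1−p̄)) + z(0.80)·√(p0(1−p0) + p1(1−p1))]² / (p1−p0)²

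With p0 = 0.265, p1 = 0.3525 and p̄ = 0.30875:

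n = [2.2414 × 0.6533 + 0.8416 × 0.6504]² / 0.0875² = 528.6, i.e. 529 per arm.

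This is 2.8% above 514, close enough to count as reproduced. Power at 514 by the same formula is 78.8% against the stated 80%. Attrition: 514/0.98 = 524.5, i.e. 525, and 3 × 525 = 1575, as stated.

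**2. Does Holm keep the overall error at 5%, with the third test included?**

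Assume the gated third test is run at 5%. With three arms and null hypotheses of equality, either all three nulls are true or at most one is.
- *All arms equal.* Any error first needs a primary rejection at 2.5%. The chance is at most 2.5% + 2.5% = 5%.
- *TLI equals undisturbed culture, both differ from standard care.* The only true null is the third, tested at 5%.
- *Exactly one arm equals standard care.* The third null is false, and the single true null is tested at no more than 5%.
- *All three arms differ.* No null is true, so no such error is possible.

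The bound is 5% in every case and does not depend on the correlation from the shared control.

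**3. Size of the gain**

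Three binomial arms of 514 with a shared control and pooled z tests were simulated, 2,000,000 trials per scenario.

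| True live birth rates (control / arm A / arm B) | Quantity | Fixed 2.5% | Holm |
|---|---|---|---|
| 26.5 / 35.25 / 35.25 | power per arm | 78.8% | 83.5% |
| | power for both | 67.1% | 76.5% |
| | power for at least one | 90.6% | 90.6% |
| 26.5 / 35.25 / 30.9 | power, arm A | 78.8% | 79.5% |
| | power, arm B | 24.5% | 33.1% |
| 26.5 / 35.25 / 26.5 | power, arm A | 78.8% | 79.0% |

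The 30.9% in the second scenario is half the planned effect: (26.5 + 35.25)/2 = 30.875. It is an assumption and is not in the documents.

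The first scenario can be checked by addition. Holm's extra rejections occur only when the other arm has already been rejected, so each one also adds to the both-arms count: 67.07 + 4.72 + 4.71 = 76.50. The chance of at least one success is 78.83 + 78.85 − 67.07 = 90.61 under either rule.

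**4. Simulated family-wise error under Holm, third test included**
- All arms equal: 4.7%.
- Both arms at 35.25%: 4.9%.
- One arm null, the other at 35.25%: 4.2%.
- One arm null, the other at 50% (chosen to approach the limit): 5.0%.

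**The case against.** The strongest reply is that nothing here is wrong. The fixed split is pre-specified, valid, stated consistently in both sections and matched to the sample size, and the planned power per comparison is essentially delivered. That stands: leaving the rule unchanged leads to no false claim.

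Several stronger readings are tempting, and the documents do not support them.
- *Holm makes the trial more likely to succeed.* Power for at least one success does not change. The primary objective asks about TLI or undisturbed culture, and on that wording Holm adds nothing.
- *The split loses power in the very scenario the design was built for.* The Study design section gives undisturbed culture, morphokinetic parameters or both as possible sources of benefit. Both arms working is one of these possibilities. If only morphokinetics helps, the gain is about 0.2 points.
- *The change is free.* Recruitment began in June 2018, so a published threshold would be relaxed during the trial. The Trial Steering Committee approves major amendments and the SAP. The statistician sees data by unlabelled arm for the monitoring committee's reports.
- *Each interval should be reported at the level at which its comparison was tested.* Levels that depend on the data lose joint coverage: in simulation about 93% to 94% (94.1% with both arms at 35.25%, 93.6% with one arm effective, 92.9% with both at 40%). Fixed 97.5% intervals hold 95.2%.

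It can also be said that Holm is not the best available method. Step-down Dunnett uses the shared-control correlation and would raise power for at least one success from 90.6% to 91.1%. That shows a further gain exists; it is no defence of plain Bonferroni. Amending before unblinded data are seen is an ordinary cost.

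**Conclusion.** A worthwhile, inexpensive gain in efficiency; not an error in the plan. With both arms effective as assumed, Holm adds about 4.7 points of power per comparison and 9.4 points for confirming both. With one arm at half the effect, that arm gains 8.6 points and the other 0.7. With one arm ineffective, the other gains almost nothing. No scenario loses power, and the 5% family-wise error is kept.

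The error bound needs only valid p values and a third test at 5% after the gate. The power figures are approximate: they use unadjusted tests on 514 independent observations per arm, whereas the plan uses covariate-adjusted logistic regression.

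**What to change.** Before any unblinded data are seen, state in the protocol or SAP:

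*The two comparisons with standard care are tested by Holm's procedure: the smaller p value at two-sided 2.5% and, if that is rejected, the other at 5%. TLI against undisturbed culture is tested at 5% only if at least one of these is rejected.*

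Keep 514 evaluable and 525 randomised per arm. Do not let the test result set the confidence level. Report either the planned 95% intervals, labelled as not adjusted for multiplicity, or 97.5% intervals for joint coverage, and take the confirmatory decision from the Holm test.

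The cost is a short amendment approved by the Trial Steering Committee, decided without reference to outcomes by arm. An interval may occasionally disagree with the Holm decision: a 95% interval can exclude no effect when nothing is rejected, and a 97.5% interval can include it when the second comparison is rejected at 5%. The first mismatch is already possible under the current plan, which pairs 95% intervals with 2.5% tests. No participants, visits or data are added.

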## Assignment of interventions: allocation

### Sequence generation {16a}

Sequence generation for randomisation will be done using a secure web-based randomisation system immediately prior to randomisation and subsequent allocation of intervention.

The randomisation will be stratified by a fertility clinic and minimised by the following:
Participant’s age (< 35 years, 35–40 years, > 40 years)Type of planned first embryo transfer (fresh, frozen).

Minimisation for both factors will include a 90% weighting to introduce 0.9 as a stochastic factor for allocation probability.

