## Data collection and management

### Plans for assessment and collection of outcomes {18a}

Trial data will be recorded by the research team at each of the participating centres directly onto trial-specific secure password-protected electronic case report forms (eCRFs) in a database administered by epiGenesys, University of Sheffield. Data that is entered directly by the embryologists (randomisation data and intervention data) will be restricted to allow access only to unblinded staff members.

The following data will be collected:
Baseline demographic data (age, ethnicity)Baseline clinical data (category of infertility, type of infertility, duration of infertility, BMI, treatment attempt, parameters of egg reserve and sperm count)Clinical treatment data (stimulation protocol, drug dosages, duration of stimulation, number of oocytes retrieved, type of insemination procedure, number of embryos available, fresh/frozen transfer, day of embryo transfer, number of embryos transferred and type of time-lapse machine, embryo grading; if applicable, documentation of morphokinetic parameters will be documented and submitted separately by embryologists to maintain blinding of the remaining study team)Data for all clinical outcomes (live birth, pregnancy test outcome, implantation, clinical pregnancy, multiple pregnancy, miscarriage, stillbirth, neonatal data)

For all participants, clinical and laboratory data are routinely recorded in the fertility medical notes or fertility electronic database by clinical staff. If clinical outcome data are not available in the medical records, a trained delegated member of the research team will phone the participants to obtain this data. Trained and delegated members of the trial team, as documented on the trial delegation log, will be responsible for the completion of the eCRFs.

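### The primary model adjusts for age only in the three minimisation bands although age itself is collected; a spline in years would gain a little precision at almost no cost

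*Protocol article*

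**What the plan says.** Under Statistical methods for primary and secondary outcomes {20a}, the article fixes the primary model: "The primary outcome (live birth) will be analysed using logistic regression model and will be adjusted for stratification and minimisation factors". It then defines those factors. The stratification factor is the clinic, and "the minimisation factors are participant’s age (< 35 years, 35–40 years, > 40 years) and type of planned first embryo transfer (fresh, frozen").

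The further covariates begin "Other covariates to be included in the analyses are treatment attempt, type of infertility (primary/secondary), category of infertility, duration of infertility, BMI" and, after the type of time-lapse equipment, end "method of insemination (IVF vs. ICSI), number of retrieved oocytes and number of available embryos". Age in years is not among them. The stated reason for the further covariates is given in the same section: "other pre-specified covariates to increase power".

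Sequence generation {16a} uses the same bands for allocation: "Participant’s age (< 35 years, 35–40 years, > 40 years"). Plans for assessment and collection of outcomes {18a} lists age as a data item in its own right: "Baseline demographic data (age, ethnicity"). Eligibility criteria {10} limits the woman's age at consent to 18 to 42, so her age must be known before randomisation.

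**The concern.** Minimisation works on categories, so age has to be banded there. A regression does not need this. As written, the model gives a woman of 35 and a woman of 40 the same age-related risk, and does the same for everyone from 18 to 34. With an upper limit of 42, the top band holds only the last two years of eligibility.

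If the chance of live birth falls with age inside a band, that gradient is left in the residual. This costs precision in both primary comparisons and in TLI versus undisturbed culture. Chance differences in age within a band also stay unadjusted; this is the same precision loss seen another way and not a bias. Since the covariates are there to raise power, the choice works slightly against its own purpose.

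**Working it through.** **1. The plan's own figure.** Inputs from Sample size {14}: p1 = 0.265, p2 = 0.3525, 2.5% per comparison (two-sided, from {20a}; z = 2.241), 80% power (z = 0.842), 514 per arm before 2% loss.

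- Pooled formula, with mean rate 0.30875: n = [2.241·√(2 × 0.30875 × 0.69125) + 0.842·√(0.265 × 0.735 + 0.3525 × 0.6475)]² / 0.0875² = (1.464 + 0.547)² / 0.007656 ≈ 529. This is 2.9% above 514; power at 514 is 78.8%.
- 514 / 0.98 = 524.5, rounded up to 525; 3 × 525 = 1575.

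The stated size is reproduced closely enough, and it does not depend on how age is coded.

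**2. Baseline for a logistic model without age.** Log odds ratio = ln[(0.3525/0.6475)/(0.265/0.735)] = ln 1.510 = 0.412. Standard error at 514 per arm = √{[1/(0.265 × 0.735) + 1/(0.3525 × 0.6475)]/514} = √(9.515/514) = 0.136. Then z = 3.03 and power = Φ(3.03 − 2.241) = 78.4%. For 80% power, 533 per arm are needed.

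**3. Parameters used.** Three bands use 2 degrees of freedom, linear age 1, a 3-knot restricted cubic spline 2 and a 4-knot spline 3. Banding therefore saves at most one parameter.

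**4. What the bands give away.** The article has no age distribution and no age-specific rates, so these are assumptions: age normal with mean 34–36 and SD 4–5, truncated to 18–42; log odds of live birth falling either by 0.05–0.12 per year throughout (steady), or by 0.02 per year below 35 and 0.10–0.25 per year from 35 (steepening). Marginal rates are held at 26.5% and 35.25%. Age is the only covariate, the test is a large-sample robust Wald test, and n per arm is for 80% power. Selected cases:

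| Mean/SD | Decline per year | Control rate at 35 → 40 | Power: bands | Power: linear | Power: correct shape | n per arm: bands → correct shape |
|---|---|---|---|---|---|---|
| 35/4 | steady 0.05 | 26% → 21% | 78.7% | 78.8% | 78.8% | 530 → 529 (0.2%) |
| 35/4 | steady 0.08 | 25% → 18% | 79.0% | 79.3% | 79.3% | 526 → 523 (0.6%) |
| 35/5 | steady 0.12 | 23% → 14% | 80.1% | 81.0% | 81.0% | 513 → 502 (2.1%) |
| 35/4 | steepening 0.10 | 28% → 19% | 78.7% | 78.7% | 78.8% | 529 → 528 (0.2%) |
| 35/4 | steepening 0.20 | 30% → 13% | 79.2% | 79.2% | 79.5% | 524 → 519 (1.0%) |
| 36/4 | steepening 0.25 | 33% → 12% | 79.8% | 79.9% | 80.4% | 517 → 509 (1.5%) |

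The gain over bands is 0.1 to 0.9 points. A linear term does no better than bands, to within 0.1 point, when the decline steepens after 35; a flexible term is needed there.

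**5. A second set of assumptions.** With mean 35, SD 4.2 and control live birth falling from 30–32% at 35 to 16%, 10% or 5.5% at 42, the saving is about 0.3%, 0.6% and 1.5% of the sample (2 to 8 per arm). A repeat of these fits gave 0.25% to 1.2%.

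**6. Scale.** The allowance for loss is 525 − 514 = 11 per arm. The largest saving in the table is 513 − 502 = 11; most are well below it.

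**The case against.** The strongest objection is that covariate coding belongs in the analysis plan, which the article promises and which is not shown. The bands in {20a} may only repeat the allocation scheme, and no sentence says that age enters in that form alone. No functional form is given for BMI, duration of infertility or the embryo counts either. Silence would indeed be no finding. Here, however, the categories are written into the sentence that defines the adjustment factors, and age is absent from the further list. The natural reading is a three-level factor. If the analysis plan already uses age in years, only the wording needs aligning.

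A second objection is that oocyte and embryo counts are in the model and would absorb the within-band gradient. This was checked by adding an age-correlated oocyte count to the second set of fits. The saving became 0.27% to 1.26% of the sample, against 0.25% to 1.2% without it. That is one assumed correlation structure, but it does not support the objection.

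Three points stand. Adjusting for the minimisation factors as used is valid. The size cannot be fixed from the document. And by span the under-35 band (18–34) is wider than 35–40, so stressing the latter presumes a steeper decline there.

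**Conclusion.** The concern holds as a minor point of efficiency. As written, {20a} enters age in three bands although age is collected, and it gives no reason to band it in the model. The cost is about 0.1 to 0.9 power points, or 0.2% to 2% of the sample, under the assumed age distributions and gradients. It would be near zero if the age gradient is shallow. No conclusion of the trial should turn on it. It is worth changing because the gain, though small, is almost free. The finding assumes that age is stored in years and not only as a band; the article lists it simply as age.

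**What to change.** Keep the three bands for minimisation. In {20a} and the analysis plan, state that the outcome models replace the three-level age factor by age in years as a restricted cubic spline with three or four knots whose positions are fixed in advance. Use the same form in the chained-equations imputation described under {20c}, so that the imputation and analysis models agree. A plain linear term is not an adequate substitute if the decline steepens after 35.

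The cost is one sentence, no new data and at most one extra degree of freedom (3 for a 4-knot spline against 2 for the bands; none extra with 3 knots). The article says that the analysis plan will be finalised before data analysis, so the change can be pre-specified there.
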